**Main outcome measure(s)::**

The primary (BMI) and secondary (body fat percentage) outcomes will be assessed at baseline and after the study using a portable electronic scale with a segmental body composition monitor. The height will be measured by a portable stadiometer.

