#### Primary and secondary outcomes

2.5.1

The primary outcome of the study will be the variation of BMI and secondary outcome will be the variation of body fat percentage.

The body weight and body fat percentage will be measured by a portable electronic scale with a segmental body composition monitor (Tanita BC-558). The height will be measured by a portable stadiometer (brand: “AlturaExata”). The waist circumference will be measured with an inextensible measure tape, with amplitude of 150 cm and variation of 0.1 mm. All the measures will be taken according the protocol designed by Gordon et al.^[35]^ Each adolescent will be evaluated 3 times: baseline—at the begging of the school-year, the second—at the middle of the school-year; and the third—at the end of the school-year. To avoid follow-up losses, schools will be visited three times in each measurement time.

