### Statistical analysis

2.6

Statistical analyses for each outcome are conducted through linear mixed models that took into account the missing data and cluster effect of the schools. The models will be used to assess the impact of treatment (nudge or control school), time (treated as continuous, in months), and the treatment-by-time interaction. In this analysis, the distribution of probabilities more suitable for the variable of interest will be verified, and also the correlation structure between repeated measurements. Data analysis will be performed using the Statistical Analysis System, version 9.4 (SAS Institute Inc, Cary, NC).

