## Discussion

3

Nudge strategies have been tested in developed countries with successful results in changing obesity-related behaviors.^[11,12,36]^ We are testing a combination of these strategies to improve adolescents’ eating and activity behaviors in schools of a low-income scenario.

In Brazil, the National School Food Program stipulates that all public schools should offer no cost daily meals for students, including fruits and vegetables on menus.^[37]^ However, data from a previous research carried out in the same locality of the present study^[25]^ indicate that a percentage of more than 30% of students do not consume the food offered at school.

Proving these low-cost nudge strategies as an effective step in changing obesity-related behaviors is an important and feasible tool to improve the consumption of school meals, in public schools in Brazil. Moreover, the inclusion of these strategies on a well-established school-based randomized trial will fill the gap in the literature to evaluate the nudge strategy in high-quality studies using real scenarios. The main study is now in progress, and the primary interventions started in July.

To the best of our knowledge, there are no studies on school nudge in Brazil. Moreover, nudge strategies to increase physical activity among children and adolescents have not been studied. The randomized controlled trial of the PAAPPAS Nudge intervention described in this protocol paper will provide data on the effects of choice architecture intervention approaches for increasing fruit and vegetable, and water consumption at the school environment among students in low-income countries, and also it is innovative in investigating the behavioral effects of environmental changes to encourage physical activity in a school setting.

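### Time is modelled as a straight line in months from a start-of-year baseline, although the article reports a July start; if July is near the mid-year visit, linear time misstates the course of the effect

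*Protocol article*

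**What the plan says.** - **Model.** Section 2.6 (Statistical analysis) uses "linear mixed models that took into account the missing data and cluster effect of the schools". The fixed effects are treatment, "time (treated as continuous, in months), and the treatment-by-time interaction".
- **Visits.** Section 2.5.1 says "Each adolescent will be evaluated 3 times: baseline—at the begging of the school-year", then "the second—at the middle of the school-year; and the third—at the end of the school-year". The abstract (Main outcome measures) says only that the "outcomes will be assessed at baseline and after the study".
- **Start of intervention.** Section 2.3 places the activities within the 2018 school-year and names no month. The Discussion adds: "The main study is now in progress, and the primary interventions started in July".

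Nothing in the article counts time from the start of the intervention, adds a change point, or treats visit as categorical.

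**The concern.** A treatment-by-time term with time in continuous months forces the arms to separate at a constant rate from the first measurement. That suits an intervention that begins at baseline. If the interventions began around the second of three visits, the expected group difference in BMI is about zero, zero, and then the full effect.

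Three things would follow:

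- The fitted monthly effect would be averaged over months without exposure.
- The model would report an effect at mid-year, before there was any.
- The mid-year measurement on every adolescent would add nothing to the treatment contrast in complete data.

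Section 2.6 also relies on the mixed model to deal with missing data. That protection assumes the mean structure is right. With a wrong time trend, even loss that is unrelated to the outcome biases the estimate.

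**Working it through.** The article gives no figure for this quantity, so there is none to reproduce. The sample size of 640 in section 2.2 is neither used nor disputed here.

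**Inputs**

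- Three visits, roughly equally spaced (section 2.5.1). Scale the baseline-to-end interval to 0, 0.5, 1.
- Correlation between repeated measures 0.5 (section 2.2). Both compound symmetry (CS) and first-order autoregressive (AR(1)) forms are used, because section 2.6 leaves the structure to be verified.
- Assumptions: the 2018 school-year lies within calendar 2018, so July is near its middle, and the mid-year measurement precedes or coincides with onset. The true group difference at the three visits is then (0, 0, d).
- Variances are per adolescent in units of σ². Adolescents are treated as independent.

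**1. What the slope estimates.** Under CS the generalised least squares slope is Σ(t − t̄)y / Σ(t − t̄)² = (0.5·y₃ − 0.5·y₁)/0.5 = y₃ − y₁. The weights are (−1, 0, +1), and they are the same under AR(1) 0.5. The mid-year visit has weight zero, and slope × duration = d, the true end-minus-baseline effect.

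**2. Mid-year and monthly effect.** The line implies a change from baseline of d/2 at mid-year, where the truth is 0. With illustrative visits at months 0, 5 and 10, the fitted rate is d/10 per month against d/5 over the exposed months, a ratio of 0.5. If the effect grows linearly from an onset at 30% to 60% of the interval, the ratio runs from 0.7 to 0.4.

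**3. Variance with complete data**

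| Contrast | CS 0.5 | AR(1) 0.5 |
|---|---|---|
| Slope × duration | 1.00 | 1.50 |
| Visit as a factor, end minus baseline | 2(1 − 0.5) = 1.00 | 2(1 − 0.25) = 1.50 |
| Change point at mid-year | 0.75 | 0.94 |

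The change-point contrast has weights (−½, −½, 1) under CS, with variance 1.5 + 2(0.125 − 0.25 − 0.25) = 0.75. Under AR(1) the weights are (−¼, −¾, 1), with variance 1.625 + 2(0.09375 − 0.0625 − 0.375) = 0.9375. So the slope's variance is 1.00/0.75 = 1.33 or 1.50/0.9375 = 1.60 times that of the change-point contrast. Visit as a factor has exactly the slope's variance.

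**4. Loss at the last visit.** Suppose 20% miss it, equally in both arms and unrelated to outcome. Under CS 0.5 the information for intercept and slope is [[1.5, 0.75], [0.75, 1.375]] with all visits and [[1.333, 0.333], [0.333, 0.333]] without the last. Weighted 0.8 and 0.2, the sum is [[1.467, 0.667], [0.667, 1.167]]. The right-hand side is 0.8 × (0.5, 1.25)d = (0.4, 1.0)d. Then

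slope × duration = (1.467 × 1.0 − 0.667 × 0.4)d / (1.467 × 1.167 − 0.667²) = 1.200d/1.267 = 0.947d.

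The same calculation gives 0.942d under CS 0.9 and 0.930d under AR(1) 0.5, so the attenuation is about 5–7%. Under CS 0.5, losses of 10% and 30% give 0.98d and 0.91d. The change-point term stays at d. Visit as a factor also stays at d, because its mean structure is unrestricted.

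**5. Visit not at the midpoint.** With the mid-year visit at 40% to 60% of the interval (CS 0.5, complete data, effect still zero there), its weight runs from −0.13 to +0.13 and the implied year-end effect from 1.05d to 0.92d.

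**The case against.** The strongest reply is that little is actually biased. With complete data and a midpoint visit, slope times duration is the end-minus-baseline difference and the test is valid. The primary outcome is the variation in BMI, not a rate after onset, so a halved monthly slope is a matter of the unit reported. This stands. A reader might infer that the trial's effect estimate is halved or its test invalid, and the documents do not support that. The attenuation that remains is modest, needs loss at the last visit or uneven spacing, and section 2.5.1 plans repeat school visits to limit losses.

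Second, the July sentence is loose. It does not say which interventions count as primary or in which arms, and the article gives no calendar. If some components began earlier, or the middle visit followed some exposure, mid-year is not a second pre-intervention measurement. This also stands, and the finding is conditional for that reason.

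Third, one might read the abstract's two time points as contradicting "Each adolescent will be evaluated 3 times" in section 2.5.1. The abstract more probably names only the endpoints, which does not exclude a mid-year visit, so no contradiction is claimed.

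Fourth, the variances ignore school clustering, although whole schools are randomised. They are relative comparisons and not losses of precision for this trial.

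What the reply does not remove is that section 2.6 positively fixes a linear time effect. That form is stated in the article, not left to an unseen analysis plan, and it fits poorly with the start date that the same article reports.

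**Conclusion.** The concern holds conditionally. If July is near the mid-year visit and that measurement does not follow onset, linear time is the wrong shape: it implies half the final effect at mid-year where there is none, gives a per-month slope of about half the post-onset rate (0.7 to 0.4 for onset at 30% to 60% of the interval), and leaves the mid-year visit unused. The year-end effect is unbiased with complete data and a midpoint visit, and attenuated by about 5–7% with 20% loss at the last visit.

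It is also tempting to conclude that dropping linear time in itself recovers the 33% or 60% of excess variance. It does not: that gain belongs only to an analysis that uses both earlier visits as pre-intervention measurements. The point merits a change to the analysis text but does not threaten the validity of the main comparison.

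**What to change.** 1. Reconcile the July start with the visit schedule: state the school-year months, the visit dates, and which interventions began in July and in which arms.
2. Replace linear time with visit as a three-level factor and its interaction with treatment. Name the treatment difference in baseline-to-end-of-year BMI change as the primary contrast. This removes the false linearity and the drop-out attenuation. It costs one extra parameter per treatment factor and brings no precision gain for that contrast in complete data.
3. Only if the mid-year visit is confirmed to precede onset, use both earlier visits as pre-intervention measurements through a change point. Set it at one common planned start date for all arms. Each school's actual start date should not be used, because it is set after randomisation and would make the model depend on how promptly schools delivered. Treating adolescents as independent, the variance falls from 1.00 to 0.75 (CS 0.5) or from 1.50 to 0.94 (AR(1) 0.5).

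All of this is wording and date-keeping and needs no new data collection. The choice between steps 2 and 3 should be recorded before outcome data are examined by arm.

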### Ethics and dissemination

2.7

The protocol was approved by the Ethics Committee of the Institute of Social Medicine (Comitê de ética do Instituto de Medicina Social—CAAE: 10471313.2.0000.5260). Written informed consent will be sent to all participants’ parents, by their children. All the researchers had access to the final trial dataset. The final dataset of the trial will be available for the researchers without names or any identification of the participants. The results of the study will be published in scientific journal and will be also sent to participants’ schools.

## Discussion

3

Nudge strategies have been tested in developed countries with successful results in changing obesity-related behaviors.^[11,12,36]^ We are testing a combination of these strategies to improve adolescents’ eating and activity behaviors in schools of a low-income scenario.

In Brazil, the National School Food Program stipulates that all public schools should offer no cost daily meals for students, including fruits and vegetables on menus.^[37]^ However, data from a previous research carried out in the same locality of the present study^[25]^ indicate that a percentage of more than 30% of students do not consume the food offered at school.

Proving these low-cost nudge strategies as an effective step in changing obesity-related behaviors is an important and feasible tool to improve the consumption of school meals, in public schools in Brazil. Moreover, the inclusion of these strategies on a well-established school-based randomized trial will fill the gap in the literature to evaluate the nudge strategy in high-quality studies using real scenarios. The main study is now in progress, and the primary interventions started in July.

To the best of our knowledge, there are no studies on school nudge in Brazil. Moreover, nudge strategies to increase physical activity among children and adolescents have not been studied. The randomized controlled trial of the PAAPPAS Nudge intervention described in this protocol paper will provide data on the effects of choice architecture intervention approaches for increasing fruit and vegetable, and water consumption at the school environment among students in low-income countries, and also it is innovative in investigating the behavioral effects of environmental changes to encourage physical activity in a school setting.

## Conclusions

4

The results of this study, if shown to be effective, will confirm the importance of incorporating environmental changes into traditional nutrition education interventions to facilitate healthier choices. Thus, the research will provide new tools to contribute to reduction of growing prevalence of obesity and poor nutrition in adolescents.
